There are a growing number of jurisdictions, such as Ireland, Iceland, Thailand, and some provinces and territories in Canada [14], where POS bans have been introduced but few studies of the impact of POS bans have been conducted. An exception is a study of the Irish legislation [14], which found that high levels of compliance (97%) were accompanied by increasing support for the law, a reduction in recall of displays among both adults (49% to 22%; p < 0.001) and young people (81% to 22%; p < 0.001), a reduction in perceived youth smoking prevalence among young people, and an increase in beliefs that the law made it easier for adults to quit smoking or for children not to initiate smoking. The study failed to find a reduction in smoking prevalence either among young people or adults. However, the short follow-up period (one month) and the small sample sizes, particularly for young people (n = 214), made it unlikely that a reduction in smoking prevalence would be detected and prevents any conclusions about the longer-term impacts of the Irish legislation being drawn.

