### Research questions

Our specific research questions are:

1. Does implementation of POS regulations in the TPMS Act in i) supermarkets alone (partial ban); and ii) all tobacco retailers (complete ban) result in changes in exposure to tobacco advertising in young people aged 12 to 17 years?

2. Is a reduction in exposure to POS advertising associated with: changes in brand awareness; perceived accessibility of tobacco; perceived prevalence of youth smoking; susceptibility to smoking; and the incidence and prevalence of smoking in young people aged 12 to 17 years?

3. Is there any evidence of socio-economic patterning in any of the attitudinal or behavioural outcomes in young people?

4. What is the association between area-level deprivation and i) levels of POS tobacco advertising and availability of cigarettes pre-and post-legislation; or ii) enforcement of the legislation when implemented?

5. Is there any evidence of a dose-response relationship between changes in exposure to POS advertising and interim and longer-term outcome measures in young people?

6. Are there any unintended adverse consequences associated with the legislation, for example, an increase in cigarette purchases from black-market sources?

7. Is there any evidence of changes in POS advertising and marketing strategies in the lead up to implementation of measures in the TPMS Act in either supermarkets or small retailers?

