## Methods/design

The study has a multi-modal before and after design and uses mixed methods to collect data in four purposively selected communities. For the purposes of the study, community is defined as the catchment areas of the secondary schools selected for study. Schools were purposively selected to reflect two levels of urbanisation (large urban vs. small town) and two levels of socio-economic deprivation (high vs. medium or low). Deprivation categories were derived from the population-weighted mean Scottish Index of Multiple Deprivation (SIMD) score for all data zones falling within the school catchment areas and the proportion of children from each school receiving free school meals. To keep the influence of school factors, other than urbanisation and deprivation, to a minimum, the selected schools were non-denominational local authority schools on mainland Scotland with an ethnic minority population of less than 10% of the school roll. In addition, schools were also selected to have a pupil roll of between 1100 and 1200.

There are four main components to the study. In each community we are conducting:

•Mapping and spatial analysis of the location and density of tobacco retail outlets.

•Tobacco advertising and marketing audits of tobacco retail outlets most used by young people, supplemented by interviews and observations with a panel of retailers in four matched communities.

•Cross-sectional school surveys of pupils, with five embedded pupil cohorts.

•Focus group interviews with purposive samples of pupils.

Data for the study components were collected at baseline between February and April 2013, prior to implementation of the legislation on 29^th^ April 2013. Follow-up data collection will be repeated annually for four years. Additional marketing audits were conducted immediately post-legislation in May 2013 to assess compliance in large retail outlets and this will be repeated in May 2015 in smaller retail outlets, following implementation of the POS legislation in smaller retailers in April 2015.

Details of the study components are as follows:

1. Annual mapping and spatial analysis studies of tobacco retail outlets

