Data governance requires that the identity of all retail sites audited and all panel participants approached to take part in an interview remain confidential. In line with these requirements all sites and participants have been assigned non-identifiable codes to retain anonymity. Identifiable data (e.g. participants, premise names and address details) are held on a separate database and will be linked to electronic data files using these non-identifiable codes. Technical reports, presentations and publications will ensure that no participants or retail premises can be identified.

3. Annual school surveys of secondary school pupils

The school survey has a repeat cross-sectional design with embedded cohorts (Additional file 1: Table S1). We hypothesise that implementation of a partial ban on POS adverting (larger retailers only) will have only a small impact on awareness and attitudes. In order to assess this assertion, baseline surveys of S2 (age 13) and S4 (age 15) pupils were conducted in each of the four study schools between February and March 2013. This survey will be repeated one year later. The impact of the Scottish partial POS ban on 13-and 15-year-olds will then be compared with the impact on a similar age group of the comprehensive POS ban in Ireland, where legislation was implemented simultaneously in both large and smaller retailers in 2011 [14].

To assess the impact on the implementation of POS legislation in smaller retailers in 2015, a second baseline survey will be conducted with all pupils (S1-6) from our study schools in February to March 2015, with repeat surveys conducted annually for two years post-implementation. This survey series will allow us to measure the impact of a comprehensive ban (supermarkets and smaller retailers) on POS advertising on behavioural outcomes including smoking incidence and prevalence, as well as on brand awareness and other attitudinal outcomes.

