### Outcome measures

A logic model provides the framework for the evaluation (see Figure 1). This proposes causal pathways that link together the implementation of the POS legislation with a set of short-term, intermediate and long-term outcomes which will be assessed by the various study components. Therefore, rather than defining primary and secondary outcomes, we have set out a timeframe within which we believe the outcomes will occur. We have classified outcomes as *short-term*, if they were likely to occur within 3 months of implementation of the legislation*; intermediate*, if they were likely to occur up to one year post-implementation; and *longer-term* if they were likely to occur more than a year post-implementation.

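### A difference between the Scottish partial-ban result (about 9–11 months after the ban) and the Irish comprehensive-ban result (one month after) cannot be attributed to ban scope

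*Protocol article*

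**What the plan says.** In the school survey part of Methods/design, the protocol hypothesises that a ban in larger retailers alone will do little to awareness and attitudes. To assess this, surveys of S2 and S4 pupils "were conducted in each of the four study schools between February and March 2013" and are to be repeated one year later. The Scottish partial-ban impact "will then be compared with the impact on a similar age group of the comprehensive POS ban in Ireland". The protocol takes that comparator from reference 14, the only Irish source it cites, and notes that the Irish law covered large and small shops at once from 2011.

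The Background reports that study's fall in display recall among "young people (81% to 22%; p < 0.001") and then gives its limits: "the short follow-up period (one month) and the small sample sizes, particularly for young people (n = 214"). The authors add there that these limits rule out conclusions about longer-term Irish effects. The section that plans the comparison does not repeat this caveat.

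The same four schools are surveyed again, in all year groups, in February to March 2015, before the ban reaches small shops, and then annually for two years.

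**The concern.** Ireland is the only comparator that the protocol names for partial against comprehensive coverage. Ireland and Scotland differ in coverage, but also in time since the ban, country and calendar period.

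A smaller Scottish change might mean that a supermarket-only ban does less. It might equally mean that a first-month effect on recall fades over the following months. A larger Scottish change might only reflect attitudes that take longer to move. The documents do not say which direction to expect, so the bias cannot be signed or corrected.

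At stake is what the study may say about whether a partial ban is a weak substitute for a full one. The authors expect policy makers in other jurisdictions to use their findings.

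**Working it through.** **1. The protocol's own use of the Irish figures.** Table 3 takes three changes from the Irish study. Its required sample sizes can be reproduced with the two-proportion formula, two-sided, power 0.80:

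n = [z(1−α/2)·√(2p̄q̄) + z(0.80)·√(p₁q₁ + p₂q₂)]² / (p₁ − p₂)², then the continuity correction n′ = (n/4)·[1 + √(1 + 4/(n|p₁ − p₂|))]².

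| Outcome | Change | Table 3 (p<.05 / p<.01) | Uncorrected | Corrected |
|---|---|---|---|---|
| Awareness | 81%–22% | 14 / 19 | 10 / 16 | 14 / 19 |
| Perceived prevalence | 62%–46% | 164 / 238 | 152 / 226 | 164 / 238 |
| Perceived access | 32%–25% | 680 / 999 | 652 / 970 | 680 / 999 |

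The corrected values match exactly. There is no arithmetic error here; the problem lies in the comparison.

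**2. Time since the ban** (30.44 days per month).
- Ireland: 1 month (Background).
- Scotland, from 29 April 2013 to 1 February 2014: 278 days, 9.1 months.
- Scotland, from 29 April 2013 to 31 March 2014: 336 days, 11.0 months.
- The Data analysis section lets the window run to April 2014: 366 days to 30 April, 12.0 months.

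The Scottish interval is therefore about 9 to 11 times the Irish one, at most 12 times.

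**3. Precision of the Irish benchmark.** The documents do not say how the 214 young people split across waves. I take 214 per wave and 107 per wave as a range, which is an assumption, and treat the waves as independent. The 95% half-width is 1.96·√[(p₁q₁ + p₂q₂)/n]. For access, p₁q₁ + p₂q₂ = 0.2176 + 0.1875 = 0.4051, and 1.96·√(0.4051/214) = 0.085.

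| Outcome | Irish change (points) | n = 214 | n = 107 | Scotland, same percentages, n = 1280 |
|---|---|---|---|---|
| Access 32–25 | 7 | ±8.5 | ±12.1 | ±3.5 |
| Perceived prevalence 62–46 | 16 | ±9.3 | ±13.2 | ±3.8 |
| Awareness 81–22 | 59 | ±7.6 | ±10.8 | ±3.1 |

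The Scottish column ignores clustering within four schools. On either split the access change includes zero (7 − 8.5 = −1.5 to 7 + 8.5 = 15.5 at n = 214). The awareness change stays large (59 − 10.8 = 48.2 at worst). Imprecision therefore matters mainly for access, whereas the timing difference affects every outcome.

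**4. The internal alternative.** The small-shop ban is dated April 2015, with no day given. From 30 April 2015 to 1 February 2016 is 277 days (9.1 months); from 1 April 2015 to 31 March 2016 is 365 days (12.0 months). The interval is thus about 9 to 12 months, close to that of the supermarket step, with the same schools, year groups and season.

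Table 2 gives 747 + 766 = 1513 S2 and S4 respondents per wave for 2015–17. Using the access percentages for illustration, that change has a half-width of 1.96·√(0.4051/1513) = ±3.2 points. Set against ±3.5 for 2013–2014, the difference between the two changes has ±√(3.5² + 3.2²) = ±4.7. Scotland against Ireland gives ±√(3.5² + 8.5²) = ±9.2 at n = 214. Both ignore clustering and any pupils who appear in more than one wave.

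**The case against.** Several points on the other side are right and limit the concern.

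- **The hypothesis does not stand or fall with Ireland.** The protocol assesses it first by the Scottish before-after surveys and only then turns to Ireland. The primary analyses in the Data analysis section do not mention Ireland.
- **The first research question is separate.** A reader might infer that it rests on the Irish contrast. It asks whether the partial ban, and then the ban in "all tobacco retailers (complete ban) result in changes in exposure to tobacco advertising in young people aged 12 to 17 years". It does not ask how the two compare, and the study's own mapping, audits and surveys answer it.
- **The outcome classes do not prove a mismatch.** It is tempting to call the Irish figure short-term and the Scottish one intermediate under the protocol's own timing scheme. But outcomes are short-term "if they were likely to occur within 3 months of implementation of the legislation"; the classes describe when effects are expected, not when they are measured. Awareness, access and perceived prevalence are intermediate outcomes, expected up to one year, and a one-month reading falls inside that window too.
- **No conclusion about scope is written down.** The text says only that the results will be compared, and further detail may sit in a fuller protocol.
- **The limits of the Irish study are disclosed** in the Background, and the Discussion admits the weakness of an uncontrolled design.
- **Ireland offers something the study cannot:** it is the only comparator in the article described as a simultaneous ban in all retailers.

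What remains is narrower. The article names a comparator and states its follow-up time, and that time does not match the Scottish one. The safeguards in the Discussion (control outcomes, dose-response, triangulation) protect the Scottish before-after inference, not a cross-country contrast. No later Irish data are mentioned.

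**Conclusion.** The point holds in limited form. The Irish comparison cannot separate ban scope from a follow-up of 1 month against about 9 to 11 months, nor from country and calendar period. It affects the partial-versus-comprehensive contrast on awareness and attitudes. It does not undermine the Scottish before-after estimates, the first research question or the evaluation as a whole.

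This rests on the comparator being the one-month estimate from reference 14. The protocol does not say so outright, but cites no other Irish source. The direction of any bias is unknown. The precision argument is secondary: it depends on the assumed split of the 214 and bears mainly on perceived access. It is a cheap improvement, not a fatal flaw.

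**What to change.** 1. Keep the Irish comparison as descriptive context. State the 1-month and 9-to-11-month follow-up times beside it, and draw no inference about ban scope from it.

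2. Add an internal contrast from surveys already planned: the S2/S4 change 2013 to 2014 (supermarket step) against the S2/S4 change 2015 to 2016 (added small-shop step). Show the cumulative 2013 to 2016 S2/S4 change as well, using the same schools, year groups and season.

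3. State the limits of that contrast. It is not fully like-for-like. The 2015 baseline is already under the partial ban, and the protocol itself expects more industry activity before full implementation, so 2015–2016 estimates only the incremental step. Calendar period still differs between the two steps. The cumulative change carries three years of secular trend. Only S2 and S4 pupils from the 2015–17 surveys are used.

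The cost is some wording and one further analysis, with no new data collection. The Irish comparison loses inferential weight. In return, the contrast no longer differs in country and hardly differs in follow-up time.

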### Intervention

The intervention to be evaluated is the prohibition of tobacco advertising at point of sale (POS) contained in Sections 1 to 3 of the Tobacco and Primary Medical Services (Scotland) Act 2010 (TPMS Act) [6]. The legislation prohibits the display of tobacco products or tobacco-related products in places where tobacco products are offered for sale and requires retailers to conceal cigarettes from general view, either by covering up cigarette gantries/dispensers or by storing cigarettes under the counter. Under the legislation, displays of tobacco products or tobacco-related products (Section 2) and prices (Section 3) are also considered to be advertisements. The overall policy objective of the legislation is to reduce the attractiveness of tobacco products among children and adolescents under the age of 18, which in turn may lead to a reduction in initiation into smoking and in the longer term a reduction in smoking prevalence. The legislation was implemented in large retail outlets (mainly supermarkets) with over 280m^2^ of internal floor area used for the display of goods and serving of customers on 29^th^ April 2013 and will be extended to the remaining smaller tobacco retail outlets in April 2015.

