ii) Discreet Audit: The discreet audit includes all tobacco retail outlets in the study communities that fall into the six categories identified above. Baseline data (February to March 2013) were collected by experienced observers, who visited all outlets in pairs to record brief information on tobacco product availability and display. The brief information included data on the visibility and placement of tobacco products within the store; whether and how tobacco products are displayed; whether and how tobacco products are actively promoted for sale (both external and internal); branding of display units and pack sizes available; most prominent brand, if any; communication and visibility of pricing information; and tobacco control signage. The audits did not require retailer co-operation and observers devised techniques to accurately recall and unobtrusively record marketing and advertising information.

The discreet audit will be repeated annually until 2017. Additional visits were made to supermarkets as part of the discreet audit in May 2013 to assess immediate compliance with the legislation. In May 2015, similar visits will be made to all small shops affected in by the legislation, in order to assess compliance amongst smaller retailers. Data collected will be used to develop a metric for POS exposure with measures developed to assess location, size, proximity and visibility of displays from key reference points such as till-points, and entrance areas. Where appropriate, measures will be developed with the aid of visual prompts, for example to indicate the relative visibility of the display. It is anticipated that POS exposure will be affected by a number of factors including increased industry activity, particularly in the lead-up to full implementation in 2015, and by retailer non-compliance (e.g. delays in removing gantries or gantries being reused for other non-tobacco products) or poor implementation (e.g. leaving sales shutters open after a sale is made). As well as assessing exposure, the audit will also assess level of compliance with both the current and new point of sale legislation, along with any evidence of strategies used to circumvent the legislation.

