### Data analysis

An advantage of adopting a spatial approach to data collection is that the various quantitative datasets can be readily integrated into a GIS. By collecting postcodes, the retail outlets, audits (retailer panel and discreet) and the school survey information will each be geographically referenced. This will enable us to integrate the data into a single database for further quantitative analysis.

The primary analyses around implementation in large retailers will focus on estimating the reduction in POS advertising between February and April 2013 (baseline) and February-to April 2014 and the relationship between POS exposure and awareness of POS advertising and changes in perceived access to tobacco and perceived youth smoking prevalence. In addition to the above, the primary analyses around implementation in smaller retailers will also examine the impact of full implementation on behavioural outcomes including purchase of tobacco products and smoking incidence and smoking prevalence. Specifically, we will:

•Examine changes in exposure to tobacco advertising, access to tobacco products and attitudes towards smoking between baseline (February to April 2015) and the same months in 2016 and 2017 for the total sample, with sub-group analyses by community deprivation, urbanisation and baseline availability of cigarettes.

•Examine changes in incidence of regular smoking and smoking prevalence between baseline (February to April 2015) and the same months in 2016 and 2017, with sub-group analyses by community deprivation, urbanisation and baseline availability of cigarettes.

•Assess if there is a of a dose-response relationship between changes in POS advertising or changes in availability of cigarettes and other study outcomes. To do this, we will create continuous dummy variables for various measures of advertising exposure which can be used in the analyses.

Given the number of outcomes we wish to examine, in the analyses we will set a higher statistical significance threshold (type I or α error) where possible.

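### The 2015–17 survey contrast starts from the partial ban, so it mainly estimates the extension to small shops, not the comprehensive ban against no ban

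*Protocol article*

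**What the plan says.** The law came in two stages. The first baseline was collected "prior to implementation of the legislation on 29^th^ April 2013", the date on which large retailers were covered. According to the Intervention section, the ban "will be extended to the remaining smaller tobacco retail outlets in April 2015".

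Under the school-survey component of Methods/design, S2 and S4 pupils are surveyed in 2013 and 2014, and all year groups (S1–S6) in 2015, 2016 and 2017. Two adjacent sentences describe the later series differently. The first is: "To assess the impact on the implementation of POS legislation in smaller retailers in 2015, a second baseline survey will be conducted with all pupils". The second is: "This survey series will allow us to measure the impact of a comprehensive ban (supermarkets and smaller retailers) on POS advertising on behavioural outcomes".

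The Data analysis section fixes the comparison for the later series: "Examine changes in exposure to tobacco advertising, access to tobacco products and attitudes towards smoking between baseline (February to April 2015" and the same months of 2016 and 2017. Incidence and prevalence of smoking have the same reference wave. No 2013 reference is named for the full ban.

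For the partial ban, the 2013–14 change is to be "compared with the impact on a similar age group of the comprehensive POS ban in Ireland". The Background describes the limits of that Irish study as "the short follow-up period (one month) and the small sample sizes, particularly for young people (n = 214".

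**The concern.** A before-after contrast estimates the change from whatever state holds at its baseline. In February–March 2015 supermarket displays had been gone for almost two years. If supermarket displays mattered, part of the comprehensive ban's effect is already in the 2015 level and cannot appear in the 2015–17 change.

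Research question 1 asks separately about the partial and the complete ban, and the abstract presents both as the study's subject. A 2015–17 change reported as the effect of the comprehensive ban would attach the wrong label to one of the main results. No analysis named in the article compares full ban with no ban.

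There is also only one wave before the small-shop step, taken about two months before it. For that period the audit section expects "increased industry activity, particularly in the lead-up to full implementation in 2015".

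**Working it through.** **1. State of the law at each wave** (dates from Intervention and Methods/design)

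| Wave | Pupils | State |
|---|---|---|
| Feb–Mar 2013 | S2, S4 | no ban |
| 2014 | S2, S4 | partial ban |
| Feb–Mar 2015 | S1–S6 | partial ban, about 22 months in |
| 2016, 2017 | S1–S6 | full ban |

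Full ban against no ban can be formed only from 2013 v 2016/2017, and only in S2 and S4. S1, S3, S5 and S6 have no survey before the supermarket ban.

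**2. The plan's own figure.** For regular smoking, 13% to 10%, Table 3 gives n = 1841 (p<.05) and 2707 (p<.01). The pooled two-proportion formula with continuity correction, two-sided, power 0.80, returns both exactly. Power is 0.989 at N = 4074 and 0.851 at N = 2037, against the stated >0.99 and >0.80. The arithmetic is sound; the issue is what the contrast estimates.

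**3. Table 3, awareness.** The change 81% to 22% is the Irish result for a ban in large and small shops together, and it is entered in the 2015–17 column. If 2015 awareness stood at 71% (Table 3's smaller scenario, borrowed here as an assumption), the contrast could show at most 71 − 22 = 49 of 81 − 22 = 59 points, or 83%. Power is not at risk; the expected change is mislabelled.

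**4. Trend in the planned contrast.** The article gives no secular trend, so these declines are assumptions. Inputs are 13% in 2015, 4074 independent pupils per wave and no ban effect. Power = Φ((d − z·s0)/s1), with d the two-year decline, s0 the pooled and s1 the unpooled SE.

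| Decline per year | 2017 level | Rejects at 0.05 | Rejects at 0.01 |
|---|---|---|---|
| 0.5 points | 12% | 0.28 | 0.11 |
| 0.75 | 11.5% | 0.54 | 0.30 |
| 1.0 | 11% | 0.79 | 0.58 |
| 1.5 | 10% | 0.99 | 0.95 |

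A decline of 1.5 points a year would by itself produce the whole planned 13%-to-10% change.

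**5. Trend in the added contrast, S2/S4 2013 v 2017.** From Table 2, N is 1280 in 2013 and 747 + 766 = 1513 in 2017; prevalence is (35 + 126)/1513 = 10.6%. The same formula with a four-year decline of 2, 3 or 4 points gives 0.43, 0.79 and 0.96. This contrast is more exposed to trend than the planned one.

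**6. Precision of the added contrast.** With the variance held at 0.106 × 0.894, SE = sqrt(0.0948 × (1/1280 + 1/1513)) = 1.17 points, and power for a 3-point effect is 0.73. Letting the variance fall with prevalence gives 0.79. Clustering is ignored.

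**7. Subtracting the 2013–15 change as a pre-trend in S2/S4.**
- 2015 v 2017 alone: SE = sqrt(2 × 0.0948/1513) = 1.12 points; power for 3 points 0.76.
- (2017 − 2015) − (2015 − 2013): SE = sqrt(5 × 0.0948/1513 + 0.0948/1280) = 1.97 points; power 0.33.

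The 2013–15 change also contains any supermarket-ban effect, so it is not a clean trend.

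**8. Ireland.** The Irish study has one month of follow-up. The Scottish 2014 wave comes about 10–11 months after the supermarket ban. The comparison therefore differs in extent of ban and in time since ban, and cannot separate them.

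**The case against.** The strongest reply is that this is one loose sentence. The sentence before it names the small-retailer purpose correctly, and Data analysis introduces the 2015–17 comparisons as analyses of implementation in smaller retailers. That stands, and it makes this a matter of label and missing contrast rather than a failed design. It does not remove the claim about the comprehensive ban, which no listed comparison supports.

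Several stronger readings are tempting and are not supported:

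- *The 2015–17 change is purely the small-shop increment.* Outcome measures places long-term outcomes more than a year after implementation, so delayed supermarket-ban effects may fall in 2015–17.
- *Any background decline will simply be credited to the law.* The Discussion admits that the design is uncontrolled and that this threatens causal inference. It plans unrelated health behaviours as an internal control, dose-response analysis, triangulation and tracking of other policies. These do not remove trend, since unrelated behaviours need not follow smoking, but the threat is not ignored.
- *The early waves are discarded.* The 2013–14 data have their own primary analysis, a synthesis across all waves is planned, and modelling detail may sit in an analysis plan not shown.
- *Lead-up industry activity is overlooked.* Annual audits measure it and research question 7 asks about it.
- *Ireland is the only partial-v-full comparison.* Research question 1 examines both stages within Scotland.

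It is also fair to object that the trend figures rest on assumed declines and mostly on alpha 0.05, while the plan intends a stricter threshold where possible. The 0.01 column shows that a stricter threshold lessens the problem without curing it.

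**Conclusion.** The statement that the 2015–17 series measures the comprehensive ban is wrong as written. The 2015 reference wave lies about 22 months into the partial ban, and the specified contrast mainly estimates the step from partial to full ban, plus any delayed supermarket effect and any trend. This follows from the article's own dates and needs no assumption.

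How far the label misleads depends on how much the supermarket ban achieved by 2015, which the article does not give. It hypothesises only a small effect on awareness and attitudes. In the 71% illustration, 10 of the 59 awareness points would be lost. The rejection probabilities rest on assumed annual declines and independent pupils, and show sensitivity to trend, not an expected error rate.

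A reader might infer that the earlier waves would repair the trend problem, or that the 2015–16 change could stand in for the full ban against the 2013–14 change. Neither follows: the 2013–15 slope contains any partial-ban effect, and 2015–16 is itself a partial-to-full step.

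**What to change.** 1. Relabel the S1–S6 contrast of 2015 with 2016 and 2017 as the effect of extending the ban to small shops, given the supermarket ban. Correct the sentence in the school-survey component, and note in Table 3 that 81% to 22% is a change from no ban to full ban.
2. Add an age-matched S2/S4 contrast of 2013 with 2016/2017 as the estimate for the whole package. State that its longer uncontrolled window makes it more exposed to trend, and read it with the internal-control outcomes and dose-response analyses.
3. Show the 2013, 2014 and 2015 S2/S4 levels descriptively, or use their slope in a sensitivity analysis only.
4. Keep the Irish comparison as context, and do not call the 2015–16 change the full-ban effect.

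The cost is wording and one extra contrast. No additional wave is needed, since all are planned; the article reports only the 2013 survey as done. The downside is that the whole-package estimate covers two year groups and is less precise, with power of about 0.73–0.79 for 3 points before any allowance for clustering, against 0.99 for the S1–S6 contrast in Table 3's scenario.
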